## Control vaccine

### Meningococcal conjugate vaccine

- 1) Ingredient: Tetravalent meningococcal polysaccharide conjugated vaccine consisting of *Neisseria meningitidis* capsular polysaccharides A, C, W-135 and Y each coupled to a carrier protein
- 2) Appearance: The diluent (sodium chloride and water for injections) is a sterile clear and colourless liquid supplied separately in a prefilled syringe or ampoule. After reconstitution, vaccine appears as a clear and colourless solution.
- 3) Dose: 0.5mL, intramuscular injection
- 4) Packaging: Supplied as a sterile lyophilized white powder or cake in a single dose vial.
- 5) Labeling: Keep original label as registered in the Philippines

6) Storage condition: protected from light, stored at +2°C to 8°C

---

#### 6.1.3 PREPARATION

The preparation and administration of the vaccines to participants enrolled into the study will only be done by the unblinded study nurse according to the procedures stipulated in this study protocol. The unblinded study nurse responsible for vaccine administration is qualified to perform this task and same will be documented by site investigator.

The licensed vaccines will be prepared before use according to the package insert. For further details please refer to the MOP.

---

#### 6.1.4 DOSING AND ROUTE OF ADMINISTRATION

Vi-DT manufactured by SK bioscience, Republic of Korea, is formulated (in both Multidose and Single dose vial) to contain purified Vi-polysaccharide 25 µg in 0.5 mL per dose. The vaccine will be administered by intramuscular injection in the left anterolateral thigh or left arm deltoid region in participants below 2 years of age, less dominant arm deltoid region in age group 2-45 years. Control vaccine will also be administered at a dose of 0.5 mL through intramuscular injection.

In case the left thigh cannot be used for vaccination due to infection, eczema or injury, the right thigh will be used for vaccination instead. If the left deltoid cannot be used for vaccine administration, the right deltoid will be used instead.

---

#### 6.1.5 DOSE ADJUSTMENTS/MODIFICATIONS/DELAYS

There is no plan of Vi-DT dose adjustment and modification during the course of study.

---

#### 6.1.6 TRACKING OF DOSE

All test vaccines, control vaccine (Meningococcal conjugate vaccine) and other EPI vaccines administered will be reported in the vaccine administration log by the Study Pharmacist/Nurse. The unblinded study monitor will ensure timeline adherence for administration of study product.

---

### 6.2 STUDY AGENT ACCOUNTABILITY PROCEDURES

Used and unused Vi-DT will be disposed at site or returned as per the guidance from the manufacturer. All Used and unused control vaccines will be disposed at the site following

reconciliation as per the site SOP. All expired vaccines will be disposed as per the site SOP (See details in the MOP).

### 6.3 STANDARD OF CARE

- Appropriate medical care and treatment to participants in need during the trial will be provided as per standard of care practice in the Philippines.
- The site investigator will conduct appropriate medical investigations deemed necessary to evaluate any medical conditions that might arise during the course of the study and ensure that participants receive appropriate care and are referred to appropriate health services as needed.

### 6.4 CONCOMITANT MEDICATIONS, TREATMENTS, AND PROCEDURES

A prescription medication is defined as a medication that can be prescribed only by an authorized/licensed physician. Medications to be reported in the Case Report form (CRF) are concomitant prescription medications, over-the-counter medications and supplements. Because all the subjects are blinded and they don't know what vaccine they are receiving, both test groups and comparator group would be restricted from receiving additional Meningococcal Vaccination as prohibited medication once they are participating in this study until the blind code is open (For test group, to keep blinding; For comparator group, to prohibit any possibility of overdose).

## 7 STUDY POPULATION

### 7.1 STRATEGIES FOR RECRUITMENT AND RETENTION

The targeted sample size is 1800, 750 each in the test arm and the rest 300 in the control arm. Study staffs will approach participants/parent(s)/LAR between Days -7 to 0 at the health facility. The enrollment venue is the clinical trial sites in the Philippines. Participants/Parent(s)/LAR with aged 6 months to 45 years visiting health centers for regular immunizations or medical check-up who may be interested in participating in the study, will be asked to go to clinical trial site during the recruitment period. The site will ensure that any advertisements used to recruit subjects (letters, pamphlets, posters, etc.) are submitted to IVI for review and approved through site IRBs

before use. Before performing any study related activity consent or assent will be collected. After vaccination, participants will be kept under observation at the study site for 30 minutes to check for any immediate adverse events. The participant/parent(s)/LAR will be given a diary card with instructions on how to fill it out.

## 7.2 CONSENT AND ASSENT PROCEDURES AND DOCUMENTATION

Informed consent is a continuing process that is initiated prior to the individual's agreeing to participate in the study and continues throughout the individual's study participation. Since as per the Philippines National ethical Guideline (For Health and Health related Research 2017) for 7 to <12 years participants verbal assent is required, The documentation of this verbal assent will be completed in source document in the form of a written description of the process and witnessed. Apart from this, parental/LAR consent form will also be completed on this 7 to <12 year old participants Assent is a process that will be initiated for individual's aged 12 to <18 years, agreeing to participate in the study and continues throughout the individual's study participation. Apart from this parental/LAR consent form will also be completed for this 12 to <18 years participants.. Participants in the age group 18 to 45 years will be asked for consent through ICF only. However in case of participants in age group 6 months to <7 years, only consent will be asked from their Parent(s)/LAR.

| Subject's Age (years) | Under 7 Years       | 7 to <12 Years              | 12 to <18 Years     | 18 Years and above |
|-----------------------|---------------------|-----------------------------|---------------------|--------------------|
| Type of Consents      | ICF [Parent(s)/LAR] | ICF [Parent(s)/LAR]         | ICF [Parent(s)/LAR] | ICF (Participant)  |
|                       | -                   | Verbal assent (Participant) | IAF (Participant)   | -                  |

Information about the risks and possible benefits of participation will be provided to the participants/parent(s)/LAR through extensive discussion. Consent/Assent forms will be EC/IRB-approved prior to their use and the participants/parent(s)/LAR will be asked to read the document for their better understanding about the study.

The investigator or designated study team member will explain the study to the participants/parent(s)/LAR and answer any questions that may arise. All participants will receive

a verbal explanation in terms suited to their comprehension of the purposes, procedures, and potential risks of the study and of their rights as research participants. The participants/parent(s)/LAR will have the opportunity to carefully go through the written consent/assent form and ask questions prior to signing. Participant/parent(s)/LAR may wish to discuss the study with family or friends before making any decision as to whether or not to participate in the study and come back later to inform the site Investigator or designee of his/her decision. For those individuals who express interest in continuing with the consent/assent process, the site investigator or designee will review the consent/assent form privately in detail with the participant/parent(s)/LAR and answer any questions.

Before signing the consent/assent, participants/parent(s)/LAR will be asked to undergo an informed consent process validation to ensure that they fully understand the purpose of the study, procedures, potential risks and their rights in this study.

If the participant's representative is illiterate (i.e. not able to read and sign the ICF), then it must be signed and dated by an impartial witness who is independent of the Investigator. A witness who signs and dates the consent form is certifying that the information in this form and any other written information had been accurately explained to and understood by the subject's parent(s)/LAR. If minor participants visit the facility with LAR then valid identity document will be asked from them showing their legal guardianship.

The participants/parent(s)/LAR will sign the informed consent/assent documents prior to any procedures being done specifically for the study. The participants/parent(s)/LAR may withdraw consent/assent at any time throughout the course of the trial. A copy of the informed consent/assent document will be handed over to the participants/parent(s)/LAR for their records. The rights, safety, and wellbeing of the participants will be protected by emphasizing that the quality of their medical care will not be adversely affected even if they decline to participate in this study.

\* For both Parental consent and Participant consent, the same consent form will be used.

### 7.3 COMPENSATION FOR PARTICIPATION

Participants will not be compensated for participation in the study. However a prorated and reasonable reimbursement will be given to the participants/parent(s)/LAR for travel expenses and time lost from work / time spent at the study site will be given as approved by IRBs.

#### 7.4 PARTICIPANT INCLUSION CRITERIA

In order to be eligible to participate in this study, any individual must meet the following criteria:

1. Healthy participants 6 months to 45 years of age at enrollment
2. Participants/Parent(s)/LAR who have voluntarily given informed consent/assent
3. Participants/Parent(s)/LAR willing to follow the study procedures of the study and available for the entire duration of the study

#### 7.5 PARTICIPANT EXCLUSION CRITERIA

An individual who meets any of the following criteria will be excluded from participation in this study:

1. Child with a congenital abnormality
2. Participant who has already received meningococcal conjugate vaccine.
3. Participant concomitantly enrolled or scheduled to be enrolled in another trial
4. Known history of immune function disorders including immunodeficiency diseases (Known HIV infection or other immune function disorders)
5. Chronic use of systemic steroids (>2 mg/kg/day or >20 mg/day prednisone equivalent for periods exceeding 10 days), cytotoxic or other immunosuppressive drugs
6. Receipt of blood or blood-derived products in the past 3 months
7. Participant with a previously ascertained or suspected disease caused by *S. Typhi* (confirmed either clinically, serologically or microbiologically)
8. Participant who has had household contact with and/or intimate exposure to an individual with laboratory-confirmed *S. Typhi*
9. Individual who has previously received a typhoid vaccine
10. Participant who has received other vaccines from 1 month prior to test vaccination or planned to receive any vaccine within 1 month (except a measles containing vaccine as per government vaccination campaign)
11. Known history or allergy to vaccines or other medications
12. History of uncontrolled coagulopathy or blood disorders
13. Any abnormality or chronic disease which in the opinion of the investigator might be detrimental for the safety of the participants and interfere with the assessment of the study objectives
14. Any female participant who is lactating, pregnant\* or planning for pregnancy during the course of study period

15. Participant/Parent(s)/LAR planning to move from the study area before the end of study period
16. As per Investigator's medical judgement individuals could be excluded from the study in spite of meeting all inclusion/exclusion criteria mentioned above

### **Temporary Contraindication**

1. Acute illness, in particular infectious disease or fever (axillary temperature  $\geq 37.5^{\circ}\text{C}$ ), within three days prior to enrollment and vaccination
  - a. This individual could be rescreened upon resolution of the above said conditions

\*Urine pregnancy test (UPT) will be performed to all female participants of childbearing age from menarche.

## **7.6 STUDY PROCEDURES**

### **7.6.1 SCREENING**

#### **Informed Consent / Assent Process**

The informed consent/assent process will be conducted as described above. The date of signature of the informed consent/assent will be entered on the eCRF.

The screening process will take place during the week prior to enrollment (Days -7 to 0). After written consent/assent are obtained, screening procedures will be performed as described in the MOP. The study staff will request the screened eligible participants/parent(s)/LAR to visit trial site for vaccination which will be considered as Day 0. A participant will be enrolled if he/she meets all inclusion and none of the exclusion criteria and his/her health status is deemed acceptable as determined by medical history, physical examination, and medical judgement of the site investigator. If participant/parent(s)/LAR agrees, screening and enrollment could be done on the same day. A study ID card will be provided to each enrolled participant.

Details of visit procedures during screening are as follows:

#### **Visit 1 - Screening visit (Days -7 to 0)**

- 1) Explain study objectives and procedures, risk and benefits to the participant /parent(s) /LAR
- 2) Perform informed consent process validation

- 3) Obtain written informed consent/assent from the participant/parent(s)/LAR. Written Informed consent/assent/verbal assent will be obtained prior to performance of any study-specific screening or evaluations
- 4) Perform screening procedures within 0 to 7 days prior to study vaccination
- 5) Collect demographics, medical history, vital signs and check for inclusion and exclusion criteria
- 6) All females volunteers of child bearing age will be screened for pregnancy with UPT and whether using any contraceptive method or not
- 7) Schedule participants for enrollment and vaccination visit (V2) at the study center within 7 days after the screening visit. If an eligible participant does not come back for V2 within the 7 days after the screening visit, screening procedures must be repeated
- 8) Screening and enrollment could be done on the same day. In this case screening related information can be captured in Visit 2 page of eCRF
- 9) Participant who does not meet the criteria for participation in this trial because of fever or acute illness, may be rescreened when these conditions have resolved. Rescreened participant will be assigned the same screening number as for the initial screening

---

#### 7.6.2 ENROLLMENT

Informed consent form will be verified by study staff and inclusion and exclusion criteria will be reviewed.

Participants will be randomized to test/control groups into three age strata of age 6 months to less than 2 years, 2 to less than 18 years, and 18 to 45 years. Participants will be attributed an enrollment number. Before randomization, medication history will be obtained, vital signs and results from physical examination, growth and development evaluations will be recorded. 5 mL of blood for the immunogenicity will be obtained prior to IP administration.

Details of visit procedures during enrollment are described below and in the MOP:

##### **Visit 2 - Enrollment and Study Vaccination (Day 0)**

- 1) Collect medical history, perform clinical examination and check concomitant therapies and record in the eCRF
- 2) Confirm eligibility of participant (include urine pregnancy test for female participants attend menarche)
- 3) Perform enrollment, randomization and attribute enrollment number to participant

- 4) Perform vaccination as per instructions of the MOP
- 5) Monitor participant for 30 min following vaccination as follows:
  - Local examination of injection site
  - Clinical examination including vital signs, general physical examination before leaving the study center 30 ( $\pm$ 5) min post vaccination
  - Record solicited and unsolicited adverse reactions (if any occurrence is there)
- 6) Schedule next visit to the study center and remind participant(s)/parent/LAR to bring the diary card at the next visit
- 7) Participant/parent(s)/LAR will be instructed to evaluate local and systemic reactions at home for 7 days post immunization (from Day 0 to Day 6 post vaccination day). Diary card 1 will be issued to record adverse events and participant/parent(s)/LAR will be instructed how to fill in the diary card 1. A thermometer and ruler will be given along with diary card to record fever and measure local reactions (e.g. diameter of redness, swelling, etc). Next clinic visit after 7 days will be scheduled. Participant/parent(s)/LAR will also be instructed to contact investigator/ study staff if needed.

---

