| Unsolicited AE          |             | X                                           |             | X       | X       |         |
| SAE                     |             | X                                           |             | X       | X       | X       |
| Diary Card Provided     |             | X (DC1)                                     |             | X (DC2) | X (DC3) |         |
| Diary Card Collected    |             |                                             |             | X (DC1) | X (DC2) | X (DC3) |
| Concomitant Medications | X           | X                                           |             | X       | X       | X*      |
| Termination Record      |             |                                             |             |         |         | X       |
| SAE Reporting           |             | To be reported at any time during the trial |             |         |         |         |

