#### **Visit 3 – Safety follow-up visit (Day 7 $\pm$ 2 day)**

- 1) Record solicited and unsolicited adverse events since the last visit in eCRF
- 2) Verify that the participant/parent(s)/LAR fill in the diary card 1 correctly
- 3) Perform clinical examination (including vital signs and general physical exam) and record in eCRF
- 4) Collect interval medical history in order to capture any AEs and SAEs through interview
- 5) Hand over the diary card 2 to be filled till day 28 post vaccination
- 6) Schedule next visit, i.e. V4 and remind the participant parent(s) or legal guardian to contact investigator/ study staff if needed

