#### **Visit 4 – Follow-up visit (Week 4, Day 28 $\pm$ 3 days)**

- 1) Check diary card 2 and confirm with participant/parent(s)/LAR before recording observations in the eCRF
- 2) Perform clinical examination including vital signs, general physical examination
- 3) Collect interval medical history in order to capture any AEs and SAEs through interview. Record any unsolicited AE, SAE, and concomitant medications in eCRF
- 4) Perform blood draw (from Adult stratum) for assessment of immune responses post vaccination
- 5) Schedule next visit i.e. V5 and hand over diary card 3 to participant/parent(s)/LAR to capture any SAEs till 24 weeks (168 days) post vaccination

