## 9.3 TIME PERIOD AND FREQUENCY FOR EVENT ASSESSMENT AND FOLLOW-UP

All participants will be observed for immediate local and systemic reactions for 30 minutes after each vaccination. For 7 consecutive days (Days 0-6) after each dose of study vaccine, the participant/parent(s)/LAR will be asked to record solicited local and systemic symptoms in the diary card. The study staff will remind participant/parent(s)/LAR of the importance of properly filling the diary cards and to return the cards at the next scheduled study visit. If they did not fill up or lost their card, the parent(s) or legal guardian will be interviewed for recall of symptoms with trained study staff during clinic visit on Day 7 after vaccination.

The occurrence of an adverse event (AE) will come to the attention of study personnel during study visits and interviews of a study participant presenting for medical care, or upon review by a study monitor.

All AEs including local and systemic reactions not meeting the criteria for SAEs will be captured on the appropriate case report form (eCRF). Information to be collected includes event description, time of onset, symptoms and physical examination findings, clinician's assessment of severity, relationship to study product (as assessed by the SI), medications given and time of resolution/stabilization of the event. All AEs occurring while on study will be documented appropriately regardless of relationship.

Changes in the severity of an AE will be documented to allow an assessment of the duration of the event at each level of severity to be performed. AEs characterized as intermittent require documentation of onset and duration of each episode.

The investigator will record all reportable events with start dates occurring any time after informed consent is obtained until the last day of study participation. At each study visit, the investigator will inquire about the occurrence of AE/SAEs since the last visit. Events will be followed for outcome information until resolution or stabilization.

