## 9.4 REPORTING PROCEDURES

### 9.4.1 ADVERSE EVENT RECORDING AND REPORTING

Adverse events, solicited AEs, and SAEs will be assessed at various study visits, documented in the source record, and recorded in the eCRF using accepted medical terms and/or the diagnosis that accurately characterize the event. When the diagnosis is known the AE term recorded in the eCRF will be the diagnosis rather than constellation of symptoms. The SI will assess all AEs for seriousness, relationship to investigational product, severity, and other possible causes.

The timeframe for the collection of adverse events (AEs) occurring from the first administration of investigational product through Visit 4 for all study groups and will be collected as well as recorded in the source document and eCRF. However SAEs will be collected and recorded throughout the study period i.e. starting from the first administration of investigational product through to the end of the trial.

When an AE has not resolved by the current visit it will be documented in the eCRF as ongoing. Documentation will include date of onset, detailed description of the event and relevant history and physical examination, severity, attribution of the AE, treatment given and date the AE improved or resolved. The medical monitor will review the AEs reported regularly and clarify with SI if there are queries. The data manager will review all AEs for consistency and provide summary of AEs to the medical monitor periodically. Non-clinically significant AEs still ongoing as the end of the study will be listed as continuing. SAEs continuing at the end of the study will be followed to resolution or stabilization. Details of AE reporting are included in the MOP.

The PI, SI, and site staff will exercise due diligence in ascertaining, accurately recording and promptly entering data on the eCRF for all AEs of all study participants. As data becomes available from the participant, the clinic and laboratories, adverse events should be recorded and entered by the site staff on regular basis. Site investigators will review, in a timely manner, the AE source data and determine the severity of the event and relation to the study agent. Site investigators will contact the study medical monitor for consultation of AEs as required.

---

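### The visit windows allow diary cards 1 and 2 to be collected before the 7-day and 28-day safety periods end, and Sections 9.3 and 9.4.1 disagree on when recording of non-serious events stops

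*Protocol*

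**What the plan says.** **Solicited events.** Section 7.6.2 (Visit 2) asks participants or parents to "evaluate local and systemic reactions at home for 7 days post immunization (from Day 0 to Day 6 post vaccination day", using diary card 1. Section 9.3 repeats the period: "For 7 consecutive days (Days 0-6) after each dose of study vaccine". The collection row of Table 2 takes card 1 back at Visit 3. Section 7.6.3 heads that visit "Safety follow-up visit (Day 7" with a tolerance of plus or minus 2 days. Table 2 marks solicited events at Visits 2 and 3 only.

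**Unsolicited events.** At Visit 3 staff are to "Hand over the diary card 2 to be filled till day 28 post vaccination". Table 2 collects card 2 at Visit 4, headed "Follow-up visit (Week 4, Day 28" with a tolerance of plus or minus 3 days. The endpoint in Sections 5.1 and 11.5.3 is unsolicited events over 4 weeks (28 days).

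**End of recording.** Section 9.4.1 covers adverse events "occurring from the first administration of investigational product through Visit 4 for all study groups". Section 9.3 has the investigator record reportable events that start at any time up to the last day of participation. After Visit 4, diary card 3 and Visit 5 capture serious events only, and Table 2 has no unsolicited entry at Visit 5.

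**The concern.** The safety endpoints are defined by fixed periods after vaccination, but data collection is tied to visits that may come before those periods end. An early visit inside the window is not a deviation, so nothing would flag the missing days. An analysis rule can discard an event with onset after Day 28. It cannot restore an event that nobody collected.

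Section 11.5.3 reports the proportion of participants with events, with 95% confidence intervals, by formulation and age stratum. Section 3.3 says these data are to support a WHO prequalification safety database. Proportions used for that purpose should match the periods they are labelled with.

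**Working it through.** **Inputs.** Solicited period Day 0 to Day 6 (Sections 7.6.2 and 9.3). Unsolicited period 28 days (Sections 5.1 and 11.5.3). Visit 3 at Day 7 ± 2 and Visit 4 at Day 28 ± 3 (Table 2, Section 7.6.3). Phase II rates after the first dose from Appendix ii: 25.88% solicited, 61.40% unsolicited within 4 weeks.

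**The plan's own figure.** Day 0 to Day 6 inclusive is 7 days, so the stated 7-day period is reproduced.

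**Visit 3.** The window is 7 − 2 = Day 5 to 7 + 2 = Day 9. A visit on Day v has min(v, 7) complete diary days behind it.

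| Visit 3 on | Complete diary days | Not fully observed |
|---|---|---|
| Day 5 | 5 | up to 2 of 7 (29%) |
| Day 6 | 6 | up to 1 of 7 (14%) |
| Day 7, 8 or 9 | 7 | 0 |

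**Visit 4.** The window is 28 − 3 = Day 25 to 28 + 3 = Day 31. The shortfall is max(0, 28 − v) days.

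| Visit 4 on | Short of Day 28 | Beyond Day 28 |
|---|---|---|
| Day 25 | 3 days (3/28 = 11%) | 0 |
| Day 26 | 2 days (7%) | 0 |
| Day 27 | 1 day (4%) | 0 |
| Day 28 | 0 | 0 |
| Day 29 to 31 | 0 | 1 to 3 days |

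These percentages are shares of days, not of events.

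**Scale, under assumptions.** The documents give neither the distribution of visit days nor that of onset days. As an extreme illustration, suppose every visit falls on the earliest permitted day, the hazard of a first event is constant, and the phase II rates (infants and toddlers) apply, with the solicited rate taken as a 7-day rate. The observed proportion is then 1 − (1 − p)^(t/T).

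- Solicited: 1 − (1 − 0.2588)^(5/7) = 0.193, that is 19.3% against 25.88%, a difference of 6.6 points.
- Unsolicited: 1 − (1 − 0.614)^(25/28) = 0.573, that is 57.3% against 61.4%, a difference of 4.1 points.

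A constant hazard probably overstates the solicited loss, because vaccine reactions tend to start early. If 0% to 10% of first solicited onsets fall on Days 5 and 6, the loss with every visit on Day 5 is 25.88% × 0 to 25.88% × 0.10, or 0 to 2.6 points. When only a fraction of participants are seen early, all these figures shrink roughly in proportion.

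**Opposite direction.** If Visit 4 were on Day 31 for everyone and no onset cut were applied, the same formula gives 1 − (1 − 0.614)^(31/28) = 0.651, which is 3.7 points above 61.4%.

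**Where missed events could go.** Card 2 is issued at Visit 3, and Visit 4 takes an interval history. A reaction starting on Day 5 or 6 after an early Visit 3 can therefore still be reported. However, Visit 4 records unsolicited and serious events, so the reaction may enter under the wrong heading. After an early Visit 4 no described procedure collects a new non-serious event.

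**The case against.** The best defence is that the early days are a tolerance and not the plan. Section 7.6.2 says the next clinic visit is to be scheduled after 7 days, which puts the intended Visit 3 after Day 6 is complete. This stands as far as it goes: the shortfall is permitted, not certain. It does not close the gap, because Table 2 and Section 7.6.3 still accept Day 5 or 6.

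A reader might infer that adverse events are definitely under-counted, or that 29% and 11% of events are lost. The documents support neither. They give no visit-day or onset distribution, and the percentages are shares of days. For unsolicited events even the direction is open unless events are cut by onset date, since late visits work the other way. Section 9.3 has onset time recorded, and such a cut is ordinary content for a statistical analysis plan, so its absence here is not a fault.

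A reader might also infer a biased comparison with control. Arms are randomised and safety assessors are blinded (Section 5.3), so there is no stated reason for early visits to differ by arm. Serious events are collected throughout and are unaffected.

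Section 9.3 might be read as rescuing the late events, since it runs to the end of participation. It conflicts with Section 9.4.1, and no procedure after Visit 4 implements it for non-serious events. Its recall interview for lost or unfilled cards cannot cover days that have not yet happened.

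**Conclusion.** The point holds as a mismatch between collection windows and endpoint periods. A compliant Visit 3 on Day 5 or 6 leaves up to 2 of 7 solicited days not observed as specified, with possible recording of later reactions as unsolicited. A compliant Visit 4 on Day 25 to 27 leaves 1 to 3 of 28 days without unsolicited capture. Sections 9.3 and 9.4.1 contradict each other on when non-serious recording ends, and the Visit 4 cut-off does not match the 28-day endpoint.

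The day counts rest only on the protocol's text. The effect on incidence cannot be determined from it. The 6.6-point and 4.1-point illustrations need every visit on the earliest day and a constant hazard, and the front-loaded range for solicited events is 0 to 2.6 points even with every Visit 3 on Day 5. The effect bears on absolute incidences and their confidence intervals. The equivalence objectives are not involved. It is worth correcting because the correction is cheap and lost days cannot be recovered at analysis.

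**What to change.** For participants still to be seen:

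1. Set the Visit 3 window so that diary card 1 is collected only once Day 6 is complete, that is Day 7 to 9.
2. Keep the Visit 4 blood-draw window. If Visit 4 falls before Day 28, add a short phone contact on or after Day 28 to complete unsolicited event capture. This has to be written in as a new procedure: the only routine call is on Day 3, and Table 2 describes phone follow-up for Visits 3 and 4 only as a lockdown measure. Leaving card 2 with the participant is not enough by itself, since the next visit is Day 168.
3. Reconcile Sections 9.3 and 9.4.1 so that both say non-serious events are collected with onset through Day 28.

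The cost is a short amendment, some Visit 3 appointments moved by one or two days, and some extra calls. The documents do not allow the numbers to be estimated. Enrolment had already begun (Section 5.2, age strata reassignment), so participants already followed stay under the old rule and the trial will contain two capture rules. The study report should therefore give, by arm, the number with Visit 3 before Day 7 and the number with Visit 4 before Day 28.
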